#### Other measures

To assess programme uptake and acceptability, recruitment and attrition rates, along with any available information on the reasons for choosing not to participate or to withdraw at each stage of the trial, will be tracked and documented.

Data associated with participant engagement with the FF programme will also be collected. These include pages visited (home/resource page, dashboard, modules, podcasts, focus board, etc), number of podcasts listened to, number of tipsheets viewed or number of downloads, activities completed within modules (percentage), and the number of goals or focus areas identified and worked toward. Acceptability of the FF programme will be assessed by self-report questionnaires on user experience (usability, usefulness and satisfaction ratings).

Quantitative and qualitative data on participant engagement with online coaching and coaching acceptability will be collected from participants in the Coaching+FF group. Engagement data includes the frequency of coaching sessions scheduled versus completed, and the percentage of coaching sessions elected by participants out of a maximum of 12. Acceptability of online coaching will be assessed by participants’ ratings on perceived ease of accessing the coach, satisfaction with the coaching support and the usefulness of the coaching sessions in enhancing their confidence to support their child and family.

Coaches’ fidelity to the coaching protocol for this study will also be examined through a random sampling of session recordings for rating by a research team member familiar with the coaching approach. Data will also be collected on time spent on coaching and associated tasks to assess feasibility. To better understand the facilitators and barriers to the delivery and implementation of online coaching and the acceptability of specific intervention elements in the context of developmental regression, separate one-on-one semi-structured interviews will be conducted with parents and coaches at post-intervention.

The schedule of enrolment, interventions and assessments is outlined in table 2.

**Table 2 T2:** Schedule of enrolment, interventions and assessments

Timepoint	Enrolment	Allocation	Post-randomisation	
	T0 (baseline)		T1 (post-intervention)	T2 (6-month follow-up)
**Enrolment**				
Eligibility screen	X			
Informed consent	X			
Randomisation		X		
**Interventions**				
Family Focus				
Family Focus+Coaching				
**Assessments**				
** *Outcomes* **				
DASS-21	X		X	X
FES	X		X	X
FQOL	X		X	X
HPAS	X		X	X
CGI-S	X		X	X
CGI-I	X		X	X
** *Other data* **				
Skill regression information	X			
Antenatal and pregnancy information	X			
Developmental history	X			
Physical and medical examination or history	X			
Support and services information	X		X	X
FF engagement				
FF acceptability				
Coaching engagement				
Coaching acceptability				

CGI-I, Clinical Global Impression Scale-Improvement; CGI-S, Clinical Global Impression Scale-Severity of illness; DASS-21, Depression Anxiety Stress Scales – short form; FES, Family Empowerment Scale; FF, Family Focus programme; FQOL, Beach Family Quality of Life Scale; HPAS, Health Promoting Activities Scale.

### Data management

Participant data recorded in REDCap will be managed by Helix (Monash University). Participant intervention engagement and usage data collected via the web application for hosting the FF programme (eg, user profile and preferences, responses entered in module activities, survey reminders and coaching requests) will be stored in a secure cloud database hosted on Amazon Web Services (AWS) infrastructure, ensuring enterprise-grade security, reliability and compliance with regional data residency requirements.

All participant data will be de-identified and assigned a unique code before being used for analysis or reporting. Data sets will be password protected and available only to personnel who have been approved through the ethics application for this study.

### Data analysis

Missing data, participant dropout and loss to follow-up will be minimised through careful trial management. Additionally, the rates of missing data on individual data collection forms will be monitored at each time point throughout the study.

The primary analyses will be undertaken on an intention-to-treat basis. Participant characteristics, participant engagement and intervention usage, and coaching acceptability will be described. A 2 (Group)× 3(Time) repeated measure ANOVA will be applied to compare continuous scores for primary and secondary outcomes between the intervention and comparison groups.

To explore possible attrition biases, we will also conduct analyses to compare retained participants and those lost after baseline assessment, using *t*-tests for continuous measures and chi-square-tests for categorical variables (eg, gender, family socioeconomic and clinical factors). Qualitative data collected using semi-structured interviews (eg, transcripts) will be examined by thematic analysis.

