**Methods and analysis:**

This study is a prospective, pragmatic randomised controlled trial comparing the effectiveness of online parent coaching plus Family Focus (Coaching+FF) to Family Focus alone (FF) for primary carers of children experiencing developmental regression. A sample of 56 families will be randomised in a 1:1 ratio. Outcomes are assessed at baseline, post-intervention and 12-month post-randomisation. The primary outcome is parental stress symptoms at post-intervention. Secondary outcomes include parental depressive and anxiety symptoms, parental engagement in health-promoting activities, family empowerment, family quality of life and child global health outcomes. The study will also examine the uptake and acceptability of specific coaching and FF components and explore the facilitators and barriers to their delivery and implementation.

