## Methods

### Study design

The study is a parallel, two-armed, superiority randomised controlled trial (RCT) that examined the effectiveness and uptake of online parent coaching combined with FF. The study is registered with the International Standard Randomised Controlled Trial Number registry (ISRCTN25513446). Data will be collected at baseline (pre-randomisation, T0), post-intervention (6-month post-randomisation, T1) and follow-up (12-month post-randomisation, T2).

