#### Sample size

This study will enrol eligible families of children seen at Monash Children’s Developmental Regression Clinic who have consented to taking part in this intervention trial.

As there was a lack of available effect size estimates for interventions targeting families of children with regression, we used effect sizes from online interventions that aimed to improve mental health, stress and well-being of parents of children with a disability or chronic medical condition.^20^ To calculate the sample size required for *F-*tests (analysis of covariance (ANCOVA) and analysis of variance (ANOVA)), G*Power 3.1.9.7 software was used.^41^ To detect a large effect (*f*= 0.5) in the primary outcome (ie, parental stress) with a power of 80% and α of 0.05 (two-tailed), a sample size of 43 parents is required. To allow an attrition of approximately 30% between baseline (T0) and follow-up assessment (T2), a sample size of 56 parents (28 per group) is required.

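### The planned 2 x 3 repeated-measures ANOVA, in its standard form, drops parents who gave the primary T1 score but missed T2, and no method is stated to keep them

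*Protocol article*

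**What the plan says.** Four statements in the protocol article bear on this.

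- **Time point.** The Abstract states: "The primary outcome is parental stress symptoms at post-intervention". Study design sets the later visits as "post-intervention (6-month post-randomisation, T1) and follow-up (12-month post-randomisation, T2").
- **Principle.** Data analysis states: "The primary analyses will be undertaken on an intention-to-treat basis".
- **Method.** The same paragraph specifies a 2 (Group) x 3 (Time) design in which a "repeated measure ANOVA will be applied to compare continuous scores for primary and secondary outcomes between the intervention and comparison groups".
- **Expected loss.** Sample size allows for "attrition of approximately 30% between baseline (T0) and follow-up assessment (T2"). It gives no figure for loss by T1.

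On missing data the article offers prevention ("Missing data, participant dropout and loss to follow-up will be minimised through careful trial management"), monitoring of missing-data rates at each time point, and t-tests and chi-square tests to "compare retained participants and those lost after baseline assessment". It mentions neither imputation nor a likelihood-based model.

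**The concern.** A classical repeated-measures ANOVA needs a complete row for each participant, and software for it deletes incomplete rows by default. With three time points in the model, a parent who answers at T1 and misses T2 leaves the analysis, although the T1 score is the primary endpoint and T2 is not. Inclusion in the primary comparison would then depend on what happens between months 6 and 12.

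Two things are at stake. One is precision, in a trial of only 56 parents. The other is bias, if those who leave after T1 differ in stress and the pattern differs by arm. Differential loss is foreseeable: one arm is offered up to twelve coaching sessions and the other up to twelve SMS or email prompts, and the Introduction cites a review in which guided digital programmes had higher completion. Comparing those retained with those lost describes the problem but does not correct an estimate.

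**Working it through.** **Inputs from the article (Sample size):** f = 0.5, power 80%, two-sided alpha 0.05, 43 parents required, 56 randomised (28 per group), about 30% loss from T0 to T2. **Assumed, because not given:** loss by T1 of 10%, 15% or 20%.

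**1. The plan's own figures.** With a noncentral F and lambda = N x f², numerator df 2, six cells and one covariate give N = 43 (lambda = 43 x 0.25 = 10.75, power 0.81). Then 43 x 1.3 = 55.9, which rounds to 56. Both figures reproduce.

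**2. Expected complete cases.** 56 x (1 - 0.30) = 39.2, so about 39 have all three scores and about 17 do not. Under the same calculation, power at f = 0.5 is 0.91 at N = 56, 0.81 at 43 and 0.76-0.77 at 39.

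**3. T1 scores discarded.**
- 10% lost by T1: 56 x 0.90 = 50.4; 50.4 - 39.2 = 11.2
- 20% lost by T1: 56 x 0.80 = 44.8; 44.8 - 39.2 = 5.6

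So about 6 to 11 parents with the primary endpoint observed would not be used.

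**4. Effect on the T1 contrast, by simulation.** Set-up: 28 per arm, correlation 0.5 between visits, 1,500 replicates. T1 stress is regressed on arm and baseline, once in everyone with a T1 score and once in three-visit completers only. Fitting the same model to both sets isolates the effect of the deletion; it is not a simulation of the 2 x 3 ANOVA itself.

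*(a) Loss completely at random, true difference 0.5 SD.* Both estimates are unbiased.

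| Loss by T1 | All T1: n, power | Completers: n, power |
|---|---|---|
| 10% | 50.3, 0.51 | 39.2, 0.42 |
| 15% | 47.6, 0.49 | 39.4, 0.42 |
| 20% | 44.8, 0.48 | 39.2, 0.44 |

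At a true 1.0 SD with 15% T1 loss, power is 0.97 against 0.93.

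*(b) Later loss depends on T1 stress in one arm, true difference 0.5 SD.* T1 loss is random. After T1, comparison-arm parents above the overall T1 median leave at three times the base rate (0.30 - d1)/(1 - d1), where d1 is the loss by T1; all others leave at half of it. For d1 = 0.15 the base rate is 0.176, so the rates are 0.53 and 0.09.

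| Loss by T1 | All T1: estimate, power | Completers: n, estimate, power |
|---|---|---|
| 10% | 0.50, 0.52 | 36.2, 0.21, 0.11 |
| 15% | 0.51, 0.50 | 37.2, 0.32, 0.18 |
| 20% | 0.50, 0.45 | 37.8, 0.38, 0.24 |

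Total loss here exceeds the planned 30%; at 15% T1 loss it is 1 - 37.2/56 = 34%. At a true 1.0 SD the completer estimates are 0.72, 0.80 and 0.885. The direction is the same throughout; the size follows the assumed pattern.

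**The case against.** **Complete-case deletion is inferred.** A reader might infer that the plan commits to a completer analysis and so contradicts its intention-to-treat statement. The documents do not support that. The article nowhere says complete cases only, and it condenses a fuller protocol; an SAP that is not shown could add multiple imputation before the ANOVA, which would keep all 56. Intention-to-treat can also mean simply analysed as randomised whatever the coaching uptake, and nothing stated departs from that. A mixed model would itself leave out parents with no post-baseline score, so 39 of 56 cannot be faulted on a standard that the replacement also misses. This stands, and it limits the point to a poor fit between the stated method and the stated principle. It does not remove the point: the article fixes a specific test and does address missing data, but names nothing that would retain partial follow-up.

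**The bias has no documented size.** A reader might also infer that the treatment effect would be roughly halved. One assumed pattern does this. Suppose comparison-arm loss is 50% above and 10% below the T1 mean, all of it after T1, with random loss in the other arm. Using the half-normal mean 0.798, the completer mean shifts by (0.25 x 0.798 - 0.45 x 0.798)/0.70 = -0.23 SD, and a true 0.50 becomes 0.27. No passage supports that 5:1 one-arm pattern or the absence of loss before T1. The plan is sized on f = 0.5, which is d = 1.0 for two equal groups; the same shift would leave 0.77. If most loss precedes T1, few T1 scores are discarded at all.

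**Mitigation is planned.** The comparison-arm prompts are described as a retention measure, all parents receive reminders, and missing data are monitored. These steps may reduce loss. They do not change what the ANOVA does with whatever loss remains.

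**Conclusion.** The concern holds in this limited form. As written, the primary method in its standard form would analyse about 39 of 56 parents at the planned 30% loss and would set aside T1 scores from parents who missed only T2. The number set aside is about 6-11 if T1 loss is 10-20%, which is an assumption.

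If loss is completely at random, the cost is a modest loss of precision and no bias. If later loss depends on T1 stress and differs by arm, the T1 contrast is biased as well; the simulated figures show that this can matter but are not a forecast. The count of 39 takes the 30% literally. The multiplication by 1.3 covers only 1 - 43/56 = 23% loss, which is a separate sample-size matter.

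**What to change.** Replace the repeated-measures ANOVA as the primary analysis with a likelihood-based mixed model for repeated measures: arm by visit, adjusted for baseline Stress, using all observed post-baseline scores, parents analysed as randomised, and the T1 contrast named as primary. ANCOVA at T1 with multiple imputation would serve equally well, and the Sample size section already mentions ANCOVA.

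Add one missing-not-at-random sensitivity analysis, such as a delta shift applied to missing values, that includes parents with no post-baseline score. This brings every randomised parent into at least one analysis. State in one sentence what intention-to-treat means here and how parents with partial follow-up enter the model. Keep the comparison of retained and lost parents as description.

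The cost is revised wording and a little more analysis work, with no extra data. Enrolment is planned to run to December 2026 and T2 follows at 12 months, so the change can be made before the outcomes are analysed.

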### Aim and objectives

This study aims to evaluate the effectiveness and uptake of a blended approach (Coaching+FF) for primary carers (hereon, ‘parents’) of children experiencing developmental regression, compared with the online programme alone (FF). By using an active comparator in this study, we aim to generate clinically relevant and realistic estimates of the effects of blending coaching and the online intervention,^31^ over and above the effects of the online intervention alone. This approach acknowledges the urgent need for support among families managing child regression concerns and provides a practical framework for evaluating new intervention strategies in this context.

In comparison to parents who engage with FF without coaching (‘comparison group’), the objectives are to determine:

The effects of Coaching+FF (‘intervention group’) on the primary outcome of parental stress symptoms.The effects of Coaching+FF (‘intervention group’) on the secondary outcomes of (1) parental anxiety and depressive symptoms, (2) family empowerment, (3) parental engagement in health-promoting activities, (4) family quality of life and (5) child’s global health outcomes.

We will also explore the proportion of parents in the FF group who transition from above to below the clinical thresholds for stress, anxiety and depressive symptoms at post-intervention. In addition, the uptake and acceptability of online parent coaching and the FF programme will be examined by assessing recruitment and retention rates, user engagement metrics, coaching uptake, programme usage data and participant feedback on perceived usefulness and satisfaction at post-intervention.

We hypothesise that, compared with parents in the FF group, parents in the Coaching+FF group will report lower levels of parental stress, anxiety and depressive symptoms, and greater improvements in family empowerment, engagement in health-promoting activities, family quality of life and child’s global health outcomes. These differences are expected to emerge at post-intervention and follow-up. Further, we anticipate that parents would find online coaching and the FF programme satisfactory and acceptable.

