### Outcomes and other measures

Outcome measures will be administered at baseline (T0), post-intervention (6 months post-randomisation, T1), and follow-up (12 months post-randomisation, T2).

The primary outcome of the study is parental stress. The self-report, seven-item Stress scale from the Depression Anxiety Stress Scales^42^-short form (DASS-21) will be used to assess nervous arousal, restlessness, impatience, irritability, overactivity and agitation. Each item is rated on a 4-point scale (0=never, 1=applied to me to some degree, or some of the time (sometimes), 2=applied to me to a considerable degree, or a good part of the time (often), or 3=applied to me very much, or most of the time (almost always)).

Secondary outcome measures include the following:

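### The two-by-three repeated-measures ANOVA has no stated test of the primary outcome, stress at 6 months, and its standard tests answer other questions

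*Protocol article*

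**What the plan says.** All references are to the protocol article; no SAP is at hand.

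- **Endpoint.** Abstract, Methods and analysis: "The primary outcome is parental stress symptoms at post-intervention". Study design defines the visits as "post-intervention (6-month post-randomisation, T1) and follow-up (12-month post-randomisation, T2", with T0 measured before randomisation.
- **Endpoint, restated.** Outcomes and other measures gives no time point: "The primary outcome of the study is parental stress". Aim and objectives says of the hypothesised arm differences: "These differences are expected to emerge at post-intervention and follow-up".
- **Analysis.** Data analysis contains one between-arm method for all continuous outcomes, with two groups and three time points: "repeated measure ANOVA will be applied to compare continuous scores for primary and secondary outcomes between the intervention and comparison groups". It does not say whether the Group effect, the interaction or a contrast decides the trial.
- **Sample size.** The calculation is said to be for F-tests, "analysis of covariance (ANCOVA) and analysis of variance (ANOVA", with f = 0.5, 80% power and two-tailed alpha 0.05. It gives 43 parents, raised to 56 for about 30% attrition by T2. ANCOVA does not appear in Data analysis.

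**The concern.** A two-arm, three-visit repeated-measures ANOVA gives two standard tests that involve the arms.

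1. **Group main effect.** This is the arm difference averaged over T0, T1 and T2. Randomisation makes the expected T0 difference zero, so including T0 pulls the estimate towards zero. Including T2 adds a time point that is not the primary one.
2. **Group by Time interaction.** This is a 2-df omnibus test. It gives no single estimate and can be significant under any non-parallel pattern, including no difference at T1 and a difference at T2.

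Neither is the T1 difference. Followed as written, the plan could declare success on the primary outcome with no effect at T1, or miss a real T1 effect because it was averaged away. Since no deciding effect is named, the choice between the two F-tests also stays open until the data are seen.

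**Working it through.** **Inputs from the article.** f = 0.5, which for two equal groups is d = 2f = 1.0; alpha 0.05 two-tailed; 43 evaluable; 56 enrolled, 1:1; about 30% attrition. Expected completers: 56 × 0.70 = 39.2, taken as 39 (19 and 20).

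**Assumptions, because the article gives no figures.** Equal SD (set to 1) at all visits; one common correlation ρ between visits, 0.3 to 0.7; complete data on the 39 for every test, so that only the choice of test differs; no true T0 difference.

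**Step 1. The plan's own sample size.** For a fixed-effects F-test, λ = f²N and the error df are N minus cells minus covariates.
- Numerator df 2, six cells, one covariate: N = 43 gives λ = 0.25 × 43 = 10.75, error df 36, power 81.0%. N = 42 gives just under 80%. So 43 is reproduced.
- Numerator df 1, two groups, one covariate, which is the form of a T1 comparison: N = 34 (power 80.6%; 33 gives 79.4%).
- Repeated-measures formulas with three visits and ρ from 0 to 0.8 give 13 to 30 (Group) or 5 to 15 (interaction), never 43.

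Among the layouts tried, 43 needs a 2-df numerator. The settings actually used are not reported, so this is inference, but the sample size does not appear to have been set for a single comparison at T1.

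**Step 2. Formulas for the competing tests.** Let the true arm differences at T0, T1, T2 be (0, d1, d2) with mean m, and let h = 19 × 20 / 39 = 9.744.
- Group: λ = m²h / [(1 + 2ρ)/3], df 1 and 37.
- Interaction: λ = h × Σ(difference − m)² / (1 − ρ), df 2 and 74.
- T1 ANCOVA adjusted for T0: λ = d1²h / (1 − ρ²), df 1 and 36.

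**Step 3. One case in full: d1 = 0.7, d2 = 0.35, ρ = 0.5.**
- m = (0 + 0.7 + 0.35)/3 = 0.35, so the Group effect estimates half the T1 effect.
- Group: λ = 0.1225 × 9.744 / 0.6667 = 1.79; power 26%.
- Interaction: Σ = 0.1225 + 0.1225 + 0 = 0.245; λ = 0.245 × 9.744 / 0.5 = 4.77; power 47%.
- ANCOVA: λ = 0.49 × 9.744 / 0.75 = 6.37; power 69%.

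**Step 4. Other patterns.** Probability of a significant result at ρ = 0.5, with the values at ρ = 0.3 and ρ = 0.7 in brackets.

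| True effect in SD (T1, T2) | Group | Interaction | T1 ANCOVA |
|---|---|---|---|
| 0.7, 0.35 | 26% (31, 22) | 47% (35, 70) | 69% (61, 85) |
| 1.0, 0.5 | 46% (55, 40) | 79% (63, 95) | 94% (89, 99) |
| 1.0, 1.0 | 70% (79, 62) | 90% (77, 99) | 94% (89, 99) |
| 1.0, 0 | 24% (28, 21) | 90% (77, 99) | 94% (89, 99) |
| 0, 0.7 | 14% (16, 13) | 59% (45, 82) | 5% (5, 5) |

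A separate simulation of 3,000 runs per scenario agreed within about one percentage point where it covered the same cases (26, 47 and 68% in the first row; 46, 79 and 93% in the second). Repeating the calculation with 21 per arm, close to the stated 43, leads to the same conclusion.

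**The case against.** **The model contains a T1 contrast.** The T0-to-T1 component of the interaction is a valid 1-df estimate of the T1 effect, because the arms are equal in expectation at baseline. This is true, and it means the model family could address T1. But the article names no such contrast. It would also be less efficient than ANCOVA: with λ = d1²h / [2(1 − ρ)] its power at ρ = 0.5 is 57% against 69% for d1 = 0.7, and 86% against 94% for d1 = 1.0.

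**An unseen SAP may settle it.** It may. The objection here, though, is to a mismatch between what the article states as endpoint and what it states as analysis, and not to missing detail. An SAP that follows the article inherits the mismatch; one that departs from it contradicts the published protocol.

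**T1 is fixed only in the abstract.** The outcomes section gives no time point and the hypothesis covers both T1 and T2. Neither passage sets a different primary time point, however, and a hypothesis about both visits does not make the three-visit average or a 2-df test the right estimate.

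**The power loss depends on the scenario.** This stands. The 26% and the halved estimate apply only if the Group effect decides. If the interaction decides and a 1.0 SD effect is sustained, the loss against ANCOVA is small at ρ = 0.5 (90% against 94%) and negligible at ρ = 0.7. Power alone would not make this a serious fault. The stronger reason is that the test can be significant with no effect at T1.

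**Conclusion.** The concern holds. The article declares a T1 endpoint and pairs it with an analysis whose standard arm tests are a three-visit average that includes the pre-randomisation score and a 2-df omnibus test. The ANCOVA cited for sizing is never planned.

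Under the assumptions above, T1 ANCOVA is at least as powerful as either standard test in every pattern examined with a T1 effect, for ρ from 0.3 to 0.7. The gap runs from almost nothing (interaction, large sustained effect, high correlation) to more than 40 percentage points (Group effect, 0.7 SD half kept at T2, ρ = 0.5). With a 0.7 SD effect at T2 only, the interaction is significant in 45 to 82% of trials while the T1 test stays at 5%. The sizes rest on assumed correlations and effect patterns; the mismatch does not. Because it governs the trial's main conclusion, it must be settled before any between-arm data are examined.

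**What to change.** In Data analysis, or in the SAP with a matching protocol amendment:

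1. Name one primary analysis: the between-arm difference in DASS-21 Stress at T1, adjusted for T0 Stress, reported with a 95% CI. Estimate it by ANCOVA, or as the T1 contrast of a linear mixed model for T1 and T2 with baseline as covariate and arm-by-visit terms.
2. Make the T2 difference from the same model secondary.
3. Use the same model for the continuous secondary outcomes, in place of the two-by-three ANOVA.
4. State the T1 time point in Outcomes and other measures, and make the sample size section refer to this same test.

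The cost is wording. T0 Stress is already collected under the schedule of assessments, and ANCOVA is already mentioned in the sample size section. At f = 0.5 a 1-df comparison needs 34 evaluable parents, before any gain from the baseline covariate. That is below the 39 expected to remain from 56, so the change does not by itself require more participants.
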